#### Computerised beads task [52]

The beads task is a measure of probabilistic reasoning which was initially designed to measure jumping to conclusion (JTC) bias in schizophrenic patients [53]. The adapted version used in this study has two parts. The first part consists of presenting two jars with beads of two different colours in different ratios (e.g. 60 orange/40 purple, and 60 purple/40 orange). Participants are told that the programme selects one of the jars to take beads randomly out of it and then return them. The instruction is to decide which jar is being used, based on the number of beads of each colour. The second part follows the same procedure with the difference being that the beads are all in white but present two different ratios of positive and negative adjectives (60 positive/40 negative, and 60 negative/40 positive). The number of beads viewed before reaching a decision is considered to be an index of jumping to conclusion bias. This procedure will be completed by participants at both pre- and post-intervention evaluations.

### Symptom measures

#### Depression, Anxiety and Stress Scale-21

The DASS [54] is a 21-item self-report questionnaire measuring symptoms of depression, anxiety, and stress. Each of the three subscales contains 7 items which, by adding up their values, provide a score for the three constructs. This questionnaire has shown good reliability with the following Cronbach’s alpha values for the Depression, Anxiety, and Stress scales, respectively: 0.84, 0.70, and 0.82 [55]. This procedure will be completed by participants at both pre- and post-intervention evaluations.

#### Patient Health Questionnaire-9

The PHQ-9 [56] is a 9-item self-report questionnaire to assess any present episodes of depression according to the DSM-IV diagnostic criteria. Each item is rated in frequency on a 4-point scale from 1 (not at all) to 4 (nearly every day). This questionnaire has shown good reliability with a Cronbach’s *α* of 0.89 [57]. An adapted PHQ-9 will also be used to measure past episodes of depression. The method of aggregation will consist in adding up the values of each item. In this study, the standard diagnostic cutoff score of PHQ-9 ≥ 10 [58] will be used to create groups based on present and past episodes of depression. This questionnaire will be completed online at pre-intervention to classify participants according to their symptom levels.

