#### Generalised Anxiety Disorder-7

Generalised Anxiety Disorder-7 [59] is a 7-item self-report questionnaire to assess any present episodes of anxiety according to the DSM-IV diagnostic criteria. Each item is rated on a 4-point scale from 0 (not at all) and 3 (nearly every day), with the final score being between 0 and 21 (calculated by adding up the values of each item). An adapted version of this questionnaire was also used to measure past episodes of anxiety. The cutoff score used in this study to consider present or past episodes of anxiety was GAD-7 ≥ 10, following the severity scale: minimal (0–4), mild (5–9), moderate (10–14), and serious (14–20) [60]. This questionnaire will be completed online at pre-intervention to classify participants according to their symptom levels.

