### Analytic plan

Demographic data and pre-treatment measures will be analysed to test for group differences with analysis of variance and chi-squared test for nominal variables.

Complete case analyses will be conducted for those participants who complete all 4 online sessions and attend pre- and post-assessment evaluation sessions. A series of 2 (group: experimental, control) × 3 (symptom group: never, present, past) × 2 (time: pre-training, post-training) analyses of variance will be performed to evaluate the change between groups. The symptom group will be created based on present and past symptoms of depression and/or anxiety to explore their influence on the results. Intention-to-treat (ITT) analyses will be conducted with all participants, regardless of session or outcome measure completion. ITT mixed models (restricted maximum likelihood (REML) estimation) will be used to account for missing data [71]. Binary logistic regression will be used to evaluate the assumption that data is Missing at Random (MAR). Exploratory mediation analyses will be conducted to study the interplay between the different cognitive bias scores given the change of the intervention. Finally, follow-up assessments will be included in a series of analyses of variance to evaluate group differences in time. All analyses will be performed in SPSS Statistics 20 with an *α* level of 0.05.

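### PHQ-9 items coded 1 to 4 and summed cannot go below 9, so the stated cutoff of 10 sits one point above the floor; item coding and cutoff must be reconciled

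*Protocol article*

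**What the plan says.** Under Patient Health Questionnaire-9, the protocol article describes an instrument that "is a 9-item self-report questionnaire to assess any present episodes of depression according to the DSM-IV diagnostic criteria". It fixes three further things:

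- Item coding: "Each item is rated in frequency on a 4-point scale from 1 (not at all) to 4 (nearly every day").
- Total score: "The method of aggregation will consist in adding up the values of each item". No subtraction or rescaling is mentioned and no score range is given.
- Classification: "the standard diagnostic cutoff score of PHQ-9 ≥ 10 [58] will be used to create groups based on present and past episodes of depression".

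An adapted PHQ-9 serves for past episodes. No separate item coding is given for it.

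Under Generalised Anxiety Disorder-7, the coding differs: "Each item is rated on a 4-point scale from 0 (not at all) and 3 (nearly every day"), with a stated total of 0 to 21 and the same numerical cutoff of 10.

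The Analytic plan crosses symptom group (never, present, past) with treatment group and time in a series of 2 × 3 × 2 complete-case analyses of variance. On how that factor is formed it says: "The symptom group will be created based on present and past symptoms of depression and/or anxiety". The stated purpose is to explore the influence of symptoms on the results.

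**The concern.** A cutoff has meaning only relative to the range of the score it is applied to. With 1-to-4 coding and a plain sum, a participant who answers 'not at all' to everything already scores 9, so a cutoff of 10 separates that single response pattern from all others. It no longer separates low from high symptom levels.

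The PHQ-9 and GAD-7 cutoffs together define one factor. Because the rule is depression and/or anxiety, a PHQ-9 case alone takes a participant out of 'never'. If the section is applied literally, the two halves of the classifier work at very different thresholds. The 'never' cells then become thin, and the symptom-group terms would describe something other than what their labels say.

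**Working it through.** **Inputs from the protocol.** PHQ-9: 9 items, codes 1 to 4, plain sum, cutoff 10, Cronbach's alpha 0.89. GAD-7: 7 items, codes 0 to 3, stated range 0 to 21, cutoff 10. Planned sample: 88. **Not given:** the share of participants scoring each PHQ-9 item above 'not at all'. This is assumed below as q = 0.1 to 0.6.

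**1. Score ranges.** Minimum = items × lowest code; maximum = items × highest code.

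- GAD-7: 7 × 0 = 0 and 7 × 3 = 21, which reproduces the stated range. The cutoff is 10 − 0 = 10 points above the floor.
- PHQ-9 as written: 9 × 1 = 9 and 9 × 4 = 36. The cutoff is 10 − 9 = 1 point above the floor. The protocol states no PHQ-9 range to compare with.
- PHQ-9 if items started at 0: range 0 to 27, cutoff 10 points above the floor. The same point on a 1-to-4 sum is 10 + 9 = 19.

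Of 4⁹ = 262,144 possible response patterns, exactly 1 falls below 10 with 1-to-4 coding. With 0-to-3 coding, 30,962 do.

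**2. A plausible correlation between items.** The mean inter-item correlation implied by alpha is α / (k − α(k − 1)) = 0.89 / (9 − 0.89 × 8) = 0.89 / 1.88 = 0.47. Treating the items as independent would contradict this. A one-factor latent-normal model with correlation ρ of 0.5 to 0.6 (assumed) is used instead:

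P(non-case) = ∫ Φ((t − √ρ·z) / √(1 − ρ))⁹ φ(z) dz, with t = Φ⁻¹(1 − q).

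**3. Share classed as present depression.** The last column also assumes that, on each item, the share of participants in the second step or higher is 0.4q and the share in the top category is 0.15q.

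| q per item | Cutoff 10, codes 1–4 | Cutoff 10, codes 0–3 |
|---|---|---|
| 0.1 | 34–39% | not computed |
| 0.2 | 54–60% | 8–9% |
| 0.3 | 68–74% | 14–15% |
| 0.4 | 79–83% | 21–22% |
| 0.5 | 86–90% | 29–30% |
| 0.6 | 92–95% | 38% |

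Independent items would give 1 − (1 − q)⁹ = 61%, 87% and 96% at q = 0.1, 0.2 and 0.3, well above the correlated results.

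**4. The 'never' level.** If the past-episode form is coded the same way, 'never' needs the lowest answer on all 18 items. The bounds below run from one common factor for both forms to forms independent of each other.

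- q = 0.3: 77–93% leave 'never', so about 88 × 0.07 = 6 to 88 × 0.23 = 20 people remain.
- q = 0.5: 91–99% leave 'never', so about 88 × 0.01 = 1 to 88 × 0.09 = 8 people remain.

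Those people are split over two arms, before attrition. GAD-7 cases can only reduce the number further.

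**5. Reach.** The sample size is based on two groups and two time points, without the symptom-group factor. No hypothesis under Objectives and hypotheses concerns symptom group. The PHQ-9 is given at pre-intervention only, to classify participants; it is not a change score.

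**The case against.** The strongest reply is that the 1-to-4 coding is a slip in describing the questionnaire. The section calls its threshold "the standard diagnostic cutoff score of PHQ-9 ≥ 10", and the companion scale is coded from 0 with the same number. If the data were scored from 0, no participant is misclassified and only the sentence is wrong. That stands as a possibility, and the document cannot settle it. The opposite is also possible. The questionnaires are completed on an online platform, so 1 to 4 could be the stored coding. With no PHQ-9 range stated, a 9-point shift would be easy to miss. Elsewhere, for the AST-D-II and the DAS, the protocol says when values are rescaled; here it does not.

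A reader might go further and infer that almost everyone becomes a depression case and the symptom-group factor collapses. The documents do not support that, for three reasons:

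- It follows only from literal application.
- It needs high item rates, which the protocol does not give, or independent items, which conflict with its own alpha.
- The plan does not say where someone meeting both the present and the past criterion is placed, so it cannot be said that 'present' absorbs everyone.

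It is also fair that the factor is exploratory. The text does not say that the intention-to-treat mixed models include it.

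**Conclusion.** The inconsistency is certain on the page: coding, summation and cutoff stand in one section and do not fit together, because the floor is 9 and the cutoff is 10. The consequence is conditional. If the rule is applied as written, about 34% to 74% would be present cases at item rates of 10% to 30%, and up to about 95% at 60%. Both the item rates and the latent correlation of 0.5 to 0.6 are assumptions. The 'never' level shrinks further if the past-episode form shares the coding.

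The harm is confined to the symptom-group terms and the cell balance of the complete-case analyses of variance. Outcome scores, random allocation, the group-by-time comparison and the sample size do not take this cutoff as an input. A correction is still needed, because a threshold that defines an analysis factor is wrong as specified and is cheap to put right.

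**What to change.** Reconcile item coding and cutoff in the Patient Health Questionnaire-9 section, state the PHQ-9 score range as is done for the GAD-7, and state the coding of the adapted past-episode form. The article reports that the study was completed by the end of 2020, so the stored coding of both forms can be checked directly.

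- If items are stored as 0 to 3, correct the sentence on coding; the groups stand.
- If items are stored as 1 to 4 and the cutoff refers to a sum of items starting at 0, as for the GAD-7, subtract 9 from the sum before applying the cutoff of 10 (equivalently, use 19 on the 1-to-4 sum). Then re-derive the symptom groups and rerun the analyses that use them.

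The cost is one check of the stored data and one corrected sentence. In the second case, add one line of scoring syntax and a rerun of the affected analyses of variance.

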#### Generalised Anxiety Disorder-7

Generalised Anxiety Disorder-7 [59] is a 7-item self-report questionnaire to assess any present episodes of anxiety according to the DSM-IV diagnostic criteria. Each item is rated on a 4-point scale from 0 (not at all) and 3 (nearly every day), with the final score being between 0 and 21 (calculated by adding up the values of each item). An adapted version of this questionnaire was also used to measure past episodes of anxiety. The cutoff score used in this study to consider present or past episodes of anxiety was GAD-7 ≥ 10, following the severity scale: minimal (0–4), mild (5–9), moderate (10–14), and serious (14–20) [60]. This questionnaire will be completed online at pre-intervention to classify participants according to their symptom levels.

### Other measures

#### Pemberton Happiness Index

The PHI [61] is an 11-item self-report questionnaire measuring general, eudaimonic, hedonic, and social well-being. All the items will be summed up to reach a general well-being measure. It has been shown to have very good reliability (*α* = .92). This procedure will be completed by participants at both pre- and post-intervention evaluations.

#### Dysfunctional Attitudes Scale

The DAS [62] is a scale of 40 sentences reflecting dysfunctional cognitive schemas. Participants have to rate each sentence from 0 (not applicable to me) to 3 (highly applicable to me). The sum of the scores is considered to be an index of stable dysfunctional attitudes (i.e. a measure of cognitive structures)*.* Inverse items will be rescaled so that higher scores reflect higher levels of dysfunctional attitudes. The DAS is a predictor of major depression [63] and it has shown to have good reliability *α* = .70 [64]. This procedure will be completed by participants at both pre- and post-intervention evaluations.

#### Ruminative Responses Scale

The RRS [60] is composed of two subscales measuring rumination cognitive style. For the present study, only the 5-item brooding subscale will be used to measure the tendency to ruminate about negative events by adding up all the items. The scale has shown good reliability (*α* = .93) [65]. This procedure will be completed by participants at both pre- and post-intervention evaluations. *The scale for mood assessment-EVEA* [66] is a measure of current mood that participants take immediately before and immediately after each of the sessions of the programme. It is included to reflect some possible reactions to the cognitive training procedure. Participants have to rate, from 0 to 10, their current level of anger, happiness, anxiety, depression, and boredom. Scores of each subscale (4 items each) are summed up providing an index of emotional change during the session.

#### Credibility and Expectancy Questionnaire

The CEQ [67] is a 6-item measure used to assess the expectancy and rationale credibility of participants regarding the online programme they are offered before they start it. It consists of two subscales that measure credibility based on cognition (*what you think*) and treatment expectancy based on affect (*what you feel*). Both subscales have shown to have good internal consistency (*α* = .86 for credibility, *α* = .90 for expectancy).

#### The Working Alliance Inventory for Internet interventions (WAI-I)

The Working Alliance Inventory for Internet interventions (WAI-I) [68] is a self-report measure to assess alliance in Internet interventions. In this study, only the 8-item subscale of task and goal agreement with the programme was used to measure the level of concordance of the programme with participants’ interests. This measure was used at the end of the programme to know if participants were satisfied with the result. An example of an item is ‘Through the online program I have become clearer about the things I need to do to help improve my situation’. Cronbach’s *α* for this subscale has been found to be good (*α* = .84) [68].

#### The Stressful Events Questionnaire (SE)

The Stressful Events Questionnaire (SE) [69] is a self-report scale to measure stressful situations that happen to participants between the second assessment and the follow-up (2 weeks and 3 months). The scale includes positive and negative ratings of high-impact events as well as daily events related to different contexts (social, emotional, academic/occupational, and ‘other’).

### Procedure

Figure 4 shows the schedule of enrolment, intervention, and assessment following the recommendations for clinical trials [70]. The main investigator will create a random sequence to assign participants to either the experimental or the control group. After the volunteers contact the main researcher for initial information about the study, they will receive a phone call from the researcher to explain the procedure of the study and the outline of the intervention programme. Participants will be given all the ethical considerations regarding their participation and will be allowed to ask any further questions. After they verbally consent to continue, they will be assigned a participation code, randomly generated to ensure anonymity. Then, participants will complete two different assessments. First, they will receive the questionnaires for the first assessment (i.e. PHQ-9, GAD-7, AST-D-II, DASS-21, DAS, RRS, PHI, and CEQ), together with the information sheet providing details of the programme. Questionnaires will be completed online, using the Qualtrics platform, to which participants will be invited via a personalised link sent to their mailbox. Second, the day after participants complete these questionnaires at home, they will attend the first session in the lab. At that moment, they will be given the consent form (explaining their right to freely withdraw from the study at any moment) and will be asked to sign it if they agree to continue. Then, the main investigator will explain in detail the rationale of the intervention ‘Relearning how to think’ and will answer any questions from the participants. If they finally agree to participate, they will be asked to sign the consent form and complete some demographic information. Then, the three experimental tasks (MCAT, computerised beads task, and recall task) will be administered.

**Fig. 4 Fig4:**
[figure not shown]
Schedule of enrolment, interventions, and assessments

After completion of the three lab tasks, participants in the experimental group will receive in their email the link to complete the online programme from home. They will need to log in to an online platform created for this study and will be invited to create their own account and password to access the materials. Information will be stored solely using the participant’s code number and only the main researchers will have access to the data. These data will be recorded in the database of the platform and will be used by the researchers to monitor if participants in the experimental group complete all four online sessions before the post-intervention evaluation. When participants first access the platform, they will find only the first session available. Access to the next session will be granted only 24 h after completing the previous one. This intermission between sessions aims to enhance participants’ processing of the contents of each session as well as to avoid cognitive overload and boredom.

After finishing the 4-session training programme, participants in the experimental group will be notified again, after approximately 10 days, for a second assessment session. The control group will be allowed to complete the intervention right after the second assessment. To improve adherence, both groups will receive a reminder for the second assessment session the day before. Finally, participants will be sent the follow-up questionnaires (AST-D-II, DASS-21, PHI, SE) twice (in the next 2 weeks and 3 months). To increase adherence during the follow-ups, participants will be sent up to a maximum of three reminders to complete questionnaires. Both groups will have the opportunity to complete a ‘feedback question’ to give their opinion about the intervention. This question will be included in the post-assessment for the experimental group and at the follow-ups for the control group.

The procedure has been approved by the university ethics committee (Ref. 2018/19-017) and has been registered (ClinicalTrials.gov NCT03987477). Moreover, it follows the recommendations for a clinical trial protocol [70].

### Analytic plan

Demographic data and pre-treatment measures will be analysed to test for group differences with analysis of variance and chi-squared test for nominal variables.

Complete case analyses will be conducted for those participants who complete all 4 online sessions and attend pre- and post-assessment evaluation sessions. A series of 2 (group: experimental, control) × 3 (symptom group: never, present, past) × 2 (time: pre-training, post-training) analyses of variance will be performed to evaluate the change between groups. The symptom group will be created based on present and past symptoms of depression and/or anxiety to explore their influence on the results. Intention-to-treat (ITT) analyses will be conducted with all participants, regardless of session or outcome measure completion. ITT mixed models (restricted maximum likelihood (REML) estimation) will be used to account for missing data [71]. Binary logistic regression will be used to evaluate the assumption that data is Missing at Random (MAR). Exploratory mediation analyses will be conducted to study the interplay between the different cognitive bias scores given the change of the intervention. Finally, follow-up assessments will be included in a series of analyses of variance to evaluate group differences in time. All analyses will be performed in SPSS Statistics 20 with an *α* level of 0.05.

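### The first-listed between-group analysis selects on session completion, which before post-test can only happen in the experimental arm, and neither it nor the ITT model is named as deciding.

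*Protocol article*

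**What the plan says.** The Analytic plan first defines a completer set: "Complete case analyses will be conducted for those participants who complete all 4 online sessions and attend pre- and post-assessment evaluation sessions". The next sentence describes the test, a 2 (group) × 3 (symptom group) × 2 (time) design in which "analyses of variance will be performed to evaluate the change between groups".

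It then adds a second approach: "Intention-to-treat (ITT) analyses will be conducted with all participants, regardless of session or outcome measure completion", using mixed models fitted by REML. On missing data it says: "Binary logistic regression will be used to evaluate the assumption that data is Missing at Random (MAR". It does not say which of the two analyses decides the efficacy question.

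The Procedure section fixes who has sessions, and when:
- After the lab tasks, "participants in the experimental group will receive in their email the link to complete the online programme from home".
- Platform data are used to "monitor if participants in the experimental group complete all four online sessions before the post-intervention evaluation".
- For the other arm, "The control group will be allowed to complete the intervention right after the second assessment".
- On the timing of post-test, "After finishing the 4-session training programme, participants in the experimental group will be notified again, after approximately 10 days, for a second assessment session".

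**The concern.** Randomisation makes the arms comparable as allocated. A rule that keeps experimental participants only if they finished every session, and has no counterpart among controls before post-test, compares a subgroup defined after randomisation with a control group not filtered in that way. If people who finish differ from people who stop in how much they would have changed anyway, the group × time contrast contains that difference as well as any programme effect.

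The planned ITT model avoids this filter, but two things weaken it as a safeguard. First, the analyses are unranked, so if they disagree nothing in the article settles which one carries the conclusion. Second, the call to post-test is described only for people who have finished the programme. Non-finishers may therefore have no post-test value, and the ITT model must infer their outcomes under MAR. The stated check on MAR cannot do that job. A logistic regression of missingness on recorded variables shows whether missingness relates to what was observed. MAR is a statement about dependence on the unobserved values given the observed ones, and the observed data cannot confirm it.

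**Working it through.** **Which arm each condition can affect before post-test**

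| Condition for the completer set | Experimental | Control |
|---|---|---|
| All 4 sessions done | can exclude | cannot sensibly apply (no access until after post-test) |
| Attends pre- and post-assessment | can exclude | can exclude |

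The one-arm selection follows from the text alone. Only its size needs assumptions.

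**The plan's own figures, used as the yardstick.** The Sample size section gives d = .43, α = 0.05, power 0.95, a minimum of 73, and 88 after adding 20%. For the group × time interaction with two time points, f = d/2 = 0.215 and λ = N·f²·2/(1 − ρ), with 1 and N − 2 degrees of freedom. The correlation ρ is not stated. With ρ = 0.5 (assumed) the smallest N is 73 (power 0.952), and 73 × 1.2 = 87.6, so 88. With 1:1 allocation that is 44 per arm. At ρ = 0.5 the SD of a change score equals the SD of a single score, since √(2(1 − 0.5)) = 1, so a bias in SDs of change can be set against .43.

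**Selection model with no true effect.** Let a normal propensity to adhere correlate r with the change score, and let the top share p of that propensity be kept. The mean change among those kept is shifted by r·k(p), where k(p) = φ(c)/p and c is the (1 − p) normal quantile.

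- p = 0.9: c = −1.282, φ = 0.1755, k = 0.195
- p = 0.8: c = −0.842, φ = 0.2800, k = 0.350
- p = 0.7: c = −0.524, φ = 0.3477, k = 0.497

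Bias of the contrast = r·[k(p experimental) − k(p control)], with k = 0 when everyone is kept:

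| Kept, exp. / control | r = 0.2 | r = 0.3 | r = 0.4 | Share of .43 |
|---|---|---|---|---|
| 80% / 100% | 0.070 | 0.105 | 0.140 | 16–33% |
| 70% / 100% | 0.099 | 0.149 | 0.199 | 23–46% |
| 70% / 90% | 0.060 | 0.091 | 0.121 | 14–28% |
| 80% / 90% | 0.031 | 0.047 | 0.062 | 7–14% |
| 70% / 80% | 0.029 | 0.044 | 0.059 | 7–14% |
| equal | 0 | 0 | 0 | 0 |

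**Effect on the test.** With 80% of 44 kept (35.2) against 44 controls, SE = √(1/35.2 + 1/44) = 0.226. At r = 0.3 the shift is 0.105/0.226 = 0.46 standard errors, and the two-sided 5% test rejects 7.5% of the time under no effect. At 80% / 90% and r = 0.3, SE = √(1/35.2 + 1/39.6) = 0.232, the shift is 0.0465/0.232 = 0.20 standard errors, and the rejection rate is about 5.5%.

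The completion rates, the retention rates and r are all assumed; the documents give none of them. A negative r reverses the sign of every entry.

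**The case against.** The best defence is that ITT on all participants is already in the plan, that sentence order in a condensed article is not a hierarchy, and that a ranking may sit in a fuller document. This stands in part: a reader who infers that the trial has no ITT analysis, or that the completer analysis is declared primary, would be wrong. It does not rescue the completer comparison, whose stated filter acts on one arm.

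Other stronger readings also go beyond the text:

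- *Controls are unselected.* They must attend both assessments, so they are selected on willingness to continue. This is why the bias shrinks once control dropout is allowed for.
- *The rule excludes every control.* Taken word for word it could, but the ANOVA that follows has a control level, so the intended meaning is clear. The criterion just needs to be stated by arm.
- *The bias must favour the programme.* This is plausible if motivated people improve more anyway, but no passage shows it. Students are offered course credits and no symptom threshold is set, so finishers with few symptoms may have little room to change.
- *ITT rests wholly on MAR.* The Procedure says when finishers are called. It does not bar others from post-test, and the ITT sentence allows for incomplete sessions. The dependence on MAR holds only for those who lack post-test data.

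**Conclusion.** The point holds in this form: the completer set selects on adherence after randomisation in the experimental arm only, on top of attendance selection in both arms, and the plan does not say whether it or the ITT model decides. The bias is of unknown sign. Under the assumptions above its magnitude runs from about zero (equal retention) through 0.03–0.06 SD (80% against 90% kept) to 0.07–0.20 SD (70–80% completion, no control loss). The top figure, 46% of the planned .43, is the extreme with no control dropout and should not be quoted as the expected bias. The zero case also assumes that finishing sessions and attending post-test select the same kind of person, which the documents do not establish.

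The MAR sentence is wrong as written whatever the size of the bias. How much the ITT result depends on MAR turns on how many non-finishers were in fact assessed, which the article does not say.

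**What to change.** 1. Name the ITT REML mixed model as the deciding analysis. Label the all-4-sessions comparison supportive, and state that the session criterion applies to the experimental arm only while attendance applies to both.
2. Replace the claim that logistic regression evaluates MAR. Use that regression to identify observed baseline predictors of missingness and include them in the mixed model. Add a delta-shift sensitivity analysis: lower the inferred improvement of experimental participants with missing outcomes by δ, over a range, and report where the conclusion changes. As a guide to scale, a missing share m moves that arm's mean by m·δ. With m = 0.2–0.3 and δ = 0.43 SD (assumed), this is 0.2 × 0.43 = 0.09 to 0.3 × 0.43 = 0.13 SD.

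Two tempting additions should be left out. Dividing the ITT effect by the share finishing all sessions requires that partial completion brings no benefit, yet each session teaches its own biases and includes practice. If 75% finish, 15% get half of a true .43 and the rest get none (assumed), ITT is 0.75 × 0.43 + 0.15 × 0.215 = 0.355, and 0.355/0.75 = 0.473, which is 10% too high. Changing when participants are invited to post-test is no longer possible, because the Trial status section reports the study as completed by December 30, 2020.

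Cost: a few sentences of analysis wording and one further sensitivity analysis, with no change to any stated number. The headline effect may be smaller than the completer figure.
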